#### Metabolic rate

The metabolic rate is assessed by trained physiologists using indirect calorimetry. Automated metabolic carts (TrueOne 2400, Parvo Medics) measure resting and postprandial metabolic rates using an open circuit system. Measurement times coincide with blood collection times: 0 h (fasting), 45 min-1 h, 3 h, and 6 h postprandial. Participants are asked to rest quietly for 5–10 min before beginning the assessment, and collection times are approximately 15–20 min. Respiratory gases are collected while participants are in a semi-reclined position, wearing a facemask that fits securely, covering the nose and mouth. The facemask is attached to a tubing assembly connected to the cart’s mixing chamber. Through the facemask, participants breathe room air, and their exhalations are trapped by the mask and directed to the mixing chamber for volume and gas analyses. Respiratory exchange ratio is calculated using observed oxygen consumption (VO_2_) and carbon dioxide (VCO_2_) production. The Weir equation with and without urinary nitrogen is also used to estimate metabolic rate. Urinary nitrogen excretion rate is estimated using reported nitrogen intake from the 24-h dietary recalls and assuming that participants are in nitrogen balance. Frayn equations for fat and carbohydrate oxidation are used to estimate substrate utilization using VO_2_ and VCO_2_ and urinary nitrogen as described above.

### Dietary intake assessments

Two dietary assessment approaches are being used in this study. First, recent intake is assessed using the ASA24™ automated self-administered 24-h recall from the National Cancer Institute of the National Institutes of Health [16]. Measuring cups and spoons are presented on-site to demonstrate serving sizes. Participants are sent unscheduled email prompts to complete self-administered 24-h dietary recalls on two weekdays and one weekend day between the scheduled study visits (approximately 10–14 d). The recall period is from midnight to midnight the day prior to receipt of the prompt. In the event that participants do not have computer or internet access, the participant is invited to complete the 24-h recall using an on-site computer.

Habitual dietary intake is assessed using the Block 2014 Food Frequency Questionnaire by NutritionQuest [17]. Estimates of frequency of consumption of certain foods over the past 12 months are used to avoid potential seasonal biases of food intake. The electronic version of the questionnaire is administered by interview with trained study personnel and measuring cups and spoons are present for estimation of serving sizes.

### Study foods

A standard pre-test meal is provided to participants for consumption between 18:00 and 19:00 the evening before the scheduled visit #2. The targets for macronutrient intake include 30% kcal from fat, 55% kcal from carbohydrates, and 15% kcal from protein. All study foods were designed by a registered dietitian, calculated using the Nutrient Data System for Research version 2014, are prepared by the WHNRC Metabolic Kitchen and Human Feeding Laboratory, are ovo-vegetarian, and omit milk, peanuts, tree nuts, finfish, shellfish, wheat or soy as potential allergens. Written food handling and safety instructions and retherming instructions are provided by the study dietitian and included with the frozen foods. Participants are shown how to record the approximate time of consumption and estimate percent consumption of each of the study foods using a provided meal checklist. Participants are instructed to return all food packaging and uneaten foods for determination of plate waste. Detailed timing, amount, and descriptions of any additional foods, drinks, supplements, or medications consumed after 19:00 are also recorded on the meal checklist. An estimate of the time of the last meal consumed prior to the pre-test meal is also recorded. Participants are also encouraged to report any symptom-based complaints related to study foods, including but not limited to gas, bloating, diarrhea, headache, or nausea.

### Mixed macronutrient meal challenge

A mixed macronutrient liquid challenge meal patterned after a similar meal developed by the European Nutrigenomics Organization [18] contains the main ingredients: palm oil, sucrose, and pasteurized liquid egg white. Xanthan gum and cellulose gum standardized with maltodextrin are added as emulsifying agents; vanilla and almond extracts and artificial butter flavoring are added to improve palatability. All participants receive a standard meal volume, which totals approximately 12 fluid oz. The target caloric load is 800 kcal, consisting of approximately 60% kcal from fat, 25% kcal from carbohydrates, and 15% kcal from protein. Baseline assessments of vital signs, resting metabolic rate, gut fermentation (breath sample), cortisol (saliva sample), blood specimens, subjective feelings of hunger and appetite, and MindWare data collection (see description below) are completed in the fasting state before the challenge meal is provided. A small volume of deionized water (60.0 mL) is provided with the challenge meal. Additional water intake is restricted until after the 0.5 h postprandial blood draw. Deionized water is then provided for ad libitum consumption throughout the remainder of the day.

A standard snack is provided after the 6 h postprandial blood draw. The snack contains limited plant-derived polyphenols or flavonoids due to the effects of these compounds on vasodilation. Similarly, it is ovo-vegetarian and does not include the potential allergens previously listed.

### Biological specimens

#### Urine

Urine is collected for 12 h overnight prior to visit #2. Participants are instructed to void the first urine at 18:00, the time that the pre-test meal is consumed. All subsequent urine is collected in a weighed 24-h urine collection jug and stored in a provided cooler on blue ice. The final urine collection occurs at 06:00, before traveling to the research center. Urine weight is recorded and processing occurs the same day. Urine is thoroughly mixed and untreated urine is stored in 2 mL and 1 mL aliquot volumes. Acidification of 10 mL urine to 0.03 M HCl is performed using 6 M HCl (Fisher Trace Element Grade) and stored in 1 mL aliquot volumes. All specimens are stored in Cryo-Store® vials at -80 °C.

#### Stool

A single stool specimen is collected within 3 d of the scheduled visit #2. Sanitary collection supplies are provided and participants receive an email reminder 3–4 d prior to the visit. The stool is kept on blue ice and transported to the research center as soon as possible, for same-day processing. The specimen is homogenized using a Stomacher® paddle blender. The specimen is frozen and scored using sharp instruments for division into Cryo-Store® vials for long-term storage at -80 °C.

#### Saliva

Saliva is collected using the SalivaBio Oral Swab method by Salimetrics®. Saliva is collected immediately before and at 30 min intervals, up to 90 min, following each of three challenges: 1) physical fitness, 2) dietary, and 3) emotional. Sterile swabs are placed in the mouth and chewed for two min. Filled swabs are returned to the salivette container, sealed, and stored at room temperature until all daily samples are collected. Samples are transferred to 4 °C refrigeration for approximately one wk, until processing. Saliva is extracted from the collection swabs by centrifugation at 1500 × g, 21 °C, for 15 min and transferred to -80 °C storage until analysis.

#### Breath

Breath samples are collected hourly throughout the research day. Participants are instructed to inhale normally and fully exhale, in an effort to completely evacuate the lungs. Breath is collected using a single patient QuinTron© collection system and analyzed in real-time for carbon dioxide, hydrogen, and methane concentrations using the QuinTron© BreathTracker™ instrumentation.

#### Blood

Certified phlebotomists collect blood by venipuncture at four time points during Visit #2: 1) fasting, 2) 0.5 h postprandial, 3) 3 h postprandial, and 4) 6 h postprandial. All blood specimens remain on wet ice for 30 min before processing, except for the following, which require room temperature: serum, Na Heparin, and K_2_ EDTA plasma for complete blood count. Serum and plasma vacutainers are centrifuged at 1300 x g at 4 °C for 10 min. Aliquots are prepared immediately and stored in Cryo-Store® vials at -80 °C until analysis.

## Laboratory methods

### Assessment of adaptive and innate immune function

Relative frequencies of specific cell types are obtained by flow cytometry (BD LSRFortessa™). Peripheral blood mononuclear cells (PBMC) are isolated from whole blood buffy coats by Ficoll density gradient centrifugation. Lymphocyte subsets are characterized based on expression of surface proteins and include: memory and naïve B cells, memory and naïve CD4+ and CD8+ T cells, regulatory T cells, type-1 helper T cells (Th1), type-2 helper T cells (Th2), type-17 helper T cells (Th17). Innate immune cells (monocytes, neutrophils, eosinophils) are enumerated in whole blood and identified by flow cytometry. T cell responses are measured in freshly isolated peripheral blood mononuclear cells cultured with anti-CD3 and anti-CD28 antibodies or isotype control antibodies for 48 h to stimulate production of Th1 (IFN-γ), Th2 (IL-13), Th17 (IL-17A) and regulatory (IL-10) T cell cytokines. Innate immune responses are measured in freshly isolated PBMC cultured with bacterial lipopolysaccharide (LPS) for 24 h to stimulate monocyte cytokine (IL-1β, TNF-α, IL-6, IL-10) production. The concentrations of cytokines in culture supernatants are quantified by electrochemiluminescent multiplex assays [Meso Scale Discovery Sector Imager 2400].

Plasma markers of inflammation including acute phase proteins (C-reactive protein and serum amyloid A), markers of vascular inflammation (ICAM-1 and VCAM-1), chemokines (eotaxin, IP-10, MDC, MCP-1), cytokines (TNF-α, IL-6, IL-10, IL-8, IL-1β), and markers of innate immune activation (neopterin and myeloperoxidase) are measured by ELISA or electrochemiluminescent multiplex assays [Meso Scale Discovery Sector Imager 2400].

### Identification of intestinal microbiota and inflammation

The relative abundances of stool bacteria are characterized by sequence analysis of the 16S ribosomal RNA genes. Microbiome analysis of raw DNA sequencing data is performed using Quantitative Insights into Microbial Ecology bioinformatics software. Neopterin and myeloperoxidase in stool samples will be measured by ELISA.

### Metabolomics

Metabolomic profiles are determined using both quantitative targeted and semi-quantitative untargeted mass spectrometric methods. Endpoints include but are not limited to non-esterified fatty acids, total fatty acids and oxylipins, endocannabinoids, NS-ceramides, sphingoid bases, bile acids, steroids, acylcarnitines, amino acids, biogenic amines, phospholipids, triglycerides, sphingomyelins, and cholesteryl esters. Prior to analyses, samples are enriched with isotopically labeled non-native analytes to be used as analytical surrogates, and samples are randomized across analytical batches, each containing a laboratory reference material to document analytical stability. Samples are randomly replicated at a rate of 5% across the study.

### Chronic stress and stress reactivity

Allostatic load is an aggregate value derived from several parameters reflecting stress exposure. Concentrations of cortisol, epinephrine, norepinephrine, and creatinine in a 12-h urine sample are determined by ELISA. Hemoglobin A1c is measured in whole blood using the Cobas® Integra® 400 plus. Dehydroepiandosterone-sulfate concentrations are determined in plasma by electrochemiluminescence using a Cobas® e411 Immunology analyzer. Other parameters included in the allostatic load score were previously described (resting blood pressure, waist: hip circumference ratio, cholesterol level, and high sensitivity C-reactive protein). Acute stress system reactivity is measured by examining autonomic nervous system and endocrine responses to the meal, physical fitness, and emotional challenge tasks.

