### Primary hypotheses

We hypothesize that diet quality, eating behavior, physical fitness, gut microbiota, and allostatic load will be the major factors correlated with phenotypic flexibility, especially the temporal sequences of systemic immune activation and inflammation and the systemic metabolome in response to a dietary challenge.We hypothesize that higher Healthy Eating Index scores, and other measures of diet quality, will be associated with lower risk of dysbiosis of the gut microbiota and in turn, lower gut inflammation. These factors will also be associated with lower systemic immune activation and inflammation in response to a mixed macronutrient challenge meal.We hypothesize that higher diet quality will be associated with lower postprandial fatty acid concentrations and other markers of inflammation (plasma metabolomics), and reduced evidence of hepatic de novo lipogenesis in response to a mixed macronutrient challenge meal.

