### Secondary hypotheses

Secondary endpoints are grouped into three categories: metabolic/physiologic impacts, neurocognitive function, and diet/lifestyle/personal characteristics. Each category is defined below according to the list of dependent variables to be included. Selected secondary a priori hypotheses are numbered following each category definition and identified by the independent variable of interest. Directionality of the hypothesized association may vary according to each independent/dependent variable combination and therefore, the expected direction of the independent variable is reported in the numbered section and the expected direction of the dependent variable is reported in the category definition (e.g. higher diet quality will be associated with higher insulin sensitivity and lower glucose concentration), see below.

The metabolic/physiologic category includes: higher insulin sensitivity, substrate switching, production of short-chain fatty acids, breath hydrogen and methane, subjective satiety, and pulmonary function; and lower glucose concentration, peripheral arterial tone, risk of dysbiosis of the gut microbiota, gut inflammation, systemic immune activation, systemic inflammation, fatty acid profiles, oxygenated metabolites, endocannabinoids, bile acid profiles, hepatic lipogenesis, triglyceridemia, appetitive hormones, and taste threshold.Higher diet quality (e.g. according to the Healthy Eating Index), modified by genotype, will be associated with metabolic/physiologic phenotypes.Healthy eating behaviors (health-related food choices motives and non-addictive eating behaviors) will be associated with metabolic/physiologic phenotypes.Dysbiosis and gut inflammation will be associated with metabolic/physiologic phenotypes.Lower postprandial bile acid responses will be associated with metabolic/physiologic phenotypes.Lower postprandial plasma fatty acid concentrations will be associated with metabolic/physiologic phenotypes.

The neurocognitive function category includes higher executive function, healthy eating behaviors, and stress system responsiveness, and lower chronic stress, allostatic load, heart rate variability, respiration variability, and nerve conductivity.

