## Higher physical activity will be associated with neurocognitive function and metabolic/physiologic phenotypes

The diet/lifestyle/personal characteristics category includes demographics, higher diet quality, nutrient status, physical activity, bone mineral density, health-related food motives, and lower body fat, waist: hip ratio, and body mass index.6.Lower stress and allostatic load will be associated with diet/lifestyle/personal characteristics, neurocognitive function, and metabolic/physiologic phenotypes.7.Higher executive function will be correlated with diet/lifestyle/personal characteristics and neurocognitive function.

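### The allostatic load score contains hsCRP and waist:hip ratio, both of which also appear among the variables it is hypothesised to relate to; leave the shared component out of the score in those analyses

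*Protocol article*

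**What the plan says.** All references are to the protocol article.

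- **Chronic stress and stress reactivity** defines allostatic load as one aggregate of urinary cortisol, epinephrine, norepinephrine and creatinine, HbA1c, DHEA-sulfate and four further items: "resting blood pressure, waist: hip circumference ratio, cholesterol level, and high sensitivity C-reactive protein".
- **Assessment of adaptive and innate immune function** gives the outcome panel: "Plasma markers of inflammation including acute phase proteins (C-reactive protein and serum amyloid A"), followed by vascular markers, chemokines, cytokines, neopterin and myeloperoxidase, 15 plasma markers in all.
- **Primary hypotheses**, first hypothesis, names five correlates and closes its list thus: "gut microbiota, and allostatic load will be the major factors correlated with phenotypic flexibility, especially the temporal sequences of systemic immune activation and inflammation".
- **Secondary hypotheses**, number 6: "Lower stress and allostatic load will be associated with diet/lifestyle/personal characteristics, neurocognitive function, and metabolic/physiologic phenotypes". The metabolic/physiologic category includes systemic inflammation, the diet/lifestyle/personal category includes waist:hip ratio, and the neurocognitive category includes allostatic load itself.
- **Metabolic rate**: "Urinary nitrogen excretion rate is estimated using reported nitrogen intake from the 24-h dietary recalls and assuming that participants are in nitrogen balance". The Frayn equations for fat and carbohydrate oxidation use that nitrogen figure with measured gas exchange.

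The article gives no rule for removing a shared component, and the Anticipated results section defers analysis-specific plans.

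**The concern.** A score that contains a variable correlates with that variable whatever the biology. The article puts hsCRP and waist:hip ratio into the predictor and lists the same measurements among the quantities the predictor is meant to explain. A test of allostatic load against CRP level or waist:hip ratio therefore does not have a true correlation of zero under the null, and its p-value has no useful meaning.

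At stake are the reported links between allostatic load and inflammation (one strand of a primary hypothesis) and between allostatic load and body shape (a secondary hypothesis). Either could be read as a finding when part or all of it is the score's arithmetic. Hypothesis 6, taken literally, also sets allostatic load against a category that lists allostatic load.

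**Working it through.** **1. The plan's own sample size.** Sample size calculations states R = 0.18, 95% power, α = 0.05 and 22 participants in each of 18 bins.

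- Fisher z, two-sided: n = ((1.960 + 1.645) / atanh(0.18))² + 3 = 395.4, rounded up to 396 = 22 × 18. The stated figure reproduces.
- Smallest significant correlation at n = 396: tanh(1.960 / √393) = 0.099.

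The article sets R = 0.18 for dietary variables, so the yardstick used here is 0.099.

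**2. Number of components, k.** The named items come to ten if creatinine counts as a component and nine if it only normalises the urinary hormones. Splitting blood pressure or cholesterol into two raises the count. I take k = 9 to 12. The scoring rule is not stated, so I show a sum of z-scores and a count of items in the top quartile. Components are assumed independent and equally weighted, so any correlation found is pure overlap.

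**3. Score against the level of one of its own components** (fasting CRP or waist:hip ratio).

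| Scoring | Formula | k = 9 | k = 12 |
|---|---|---|---|
| z-sum | 1/√k | 0.333 | 0.289 |
| Quartile count | 0.734/√k | 0.245 | 0.212 |

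The probability of significance at n = 396 is essentially 100% for the z-sum, and 99.9% (k = 9) and 98.9% (k = 12) for the count. A simulation of the count (4,000 studies of 396) gave mean correlations of 0.24 and 0.21, significant in 99.9% and 99.1%.

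**4. The same simulation with the component left out.** The mean correlation is 0.00 and about 5% of studies are significant, the nominal level.

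**5. Other forms of the inflammation outcome.**

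- *Equally weighted mean of 15 independent markers, one of them CRP.* Divide by √15 = 3.873: from 0.212/3.873 = 0.055 to 0.333/3.873 = 0.086. Significant in about 19 to 40% of studies.
- *Post-meal CRP level.* Multiply by the fasting/post-meal correlation ρ, assumed 0.80 to 0.99: from 0.80 × 0.212 = 0.17 to 0.99 × 0.333 = 0.33.
- *Change in CRP from fasting, equal variances.* corr(change, fasting) = −√((1 − ρ)/2), which is −0.316 at ρ = 0.80 and −0.071 at ρ = 0.99. Multiplied by the step 3 values, the artefact runs from −0.105 (−0.316 × 0.333) to −0.015 (−0.071 × 0.212). Only the extreme end reaches the 0.099 threshold.

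**6. Nitrogen term (minor).** All inputs here are assumptions: fat oxidation = 1.67(VO2 − VCO2) − 1.92N, VO2 0.25 L/min, SD of the respiratory exchange ratio 0.05, SD of recalled protein 30 g/d.

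- SD of N = 30/6.25/1440 = 0.00333 g/min; times 1.92 = 0.0064.
- SD of the gas term = 1.67 × 0.25 × 0.05 = 0.0209.
- Induced correlation of recalled protein with fat oxidation = −0.0064/√(0.0209² + 0.0064²) = −0.29 (−0.12 to −0.65 across less and more extreme inputs).
- For a diet-quality score correlated 0.1 to 0.3 with recalled protein: −0.03 to −0.09.
- If one nitrogen value serves all time points, the term cancels from the pre-to-post change.

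**The case against.** **The primary outcome is a response.** The first primary hypothesis stresses temporal sequences after the meal, and the sample size section speaks of responses. For change in CRP the artefact is weak and runs against the expected direction (lower load with lower inflammation). CRP is also one of 15 plasma markers, and allostatic load is one of five named correlates. A reader might infer that the score's arithmetic could confirm the primary hypothesis; the documents do not support that. The objection stands as a limit on size. It does not remove the overlap for CRP level, or for waist:hip ratio, which is not a response measure.

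**Deferred detail.** Analysis-specific plans are to be published later, and no regression of CRP on allostatic load is fixed here. But the score's composition and the hypotheses are stated in this article, and as stated they overlap. Settling the exclusion before analysis also avoids a choice that could look data-driven.

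**Other overlaps that might be inferred.**

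- *HbA1c with glucose.* These are separate assays, so their association is biology and not a shared term.
- *Substrate oxidation derived from recalled diet.* Only the nitrogen term is. VO2 and VCO2 are measured, and the respiratory exchange ratio uses no diet data. The article also does not say whether the recalls or the food frequency questionnaire feed the diet-quality score.
- *Predictors inside their own outcome category*, as in "Dysbiosis and gut inflammation will be associated with metabolic/physiologic phenotypes", where that category lists both. This is mostly shorthand from grouping variables, and nothing shows a plan to relate a variable to itself.

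**Conclusion.** The concern holds in a limited form. With the score as defined, an analysis against CRP level or waist:hip ratio carries a built-in correlation of about 0.21 to 0.33, well above the 0.099 needed for significance at N = 396, and would be significant in about 99 to 100% of studies with no biological link. For a 15-marker average the artefact is about 0.05 to 0.09; for meal-induced change in CRP it is about −0.015 to −0.105. It therefore biases specific associations and does not by itself decide the primary hypothesis.

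The overlap itself follows from the article's definitions. Its size rests on the assumed component count, scoring rule, equal weights and independence, and for change on the assumed ρ. The times at which CRP is assayed are not given in the text; Fig. 1, which shows planned assays by time point, was not available for this check. The nitrogen term is a side issue, relevant mainly to recalled protein against absolute oxidation rates.

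**What to change.** State in the analysis plan, before analysis, that:

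1. allostatic load is computed without hsCRP in every analysis of an inflammatory outcome that includes CRP;
2. it is computed without waist:hip ratio in analyses of that ratio or of body composition (for body fat and BMI this is a precaution, since they are separate measurements);
3. the full score is used only where nothing is shared;
4. allostatic load is removed from the neurocognitive outcomes when it is the predictor.

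As a minor addition, where recall-based diet variables, especially protein, are related to fat or carbohydrate oxidation, report as a sensitivity analysis either the respiratory exchange ratio, which is already calculated, or oxidation without the recall-derived nitrogen term.

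The cost is recomputing one score in reduced versions and a few lines of text. No new data are needed. The reduced scores are slightly less comparable with the full score, so each table should name the version used.
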